### Interim analyses {21b}

Not applicable.

Interim analysis is not planned.

### Methods for additional analyses (e.g., subgroup analyses) {20b}

Not applicable.

Additional analysis is not planned.

### Methods in analysis to handle protocol non-adherence and any statistical methods to handle missing data {20c}

No analysis populations are defined for this study. Protocol non-adherence will be assessed by the principal investigator case by case. Patients with major deviations from the study protocol will be excluded from the analysis.

Missing data are not planned to be imputed. However, in the event of substantial missing data for any parameter, a sensitivity analysis using any method of imputation could also be used.

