### Sample size {14}

Studies focused on the primary target of our study are lacking. However, we have identified several studies comparing bolus and continuous administration of enteral feeding. These studies included small numbers of patients, were conducted in different patient populations, and did not assess the time to reach the nutritional targets as a primary outcome. However, for calculation of the sample size, we hypothesized a difference of 1 day between groups (target being reached on day 2 and day 3, respectively). The alpha was set to 5%, and the power was set to 80%. The estimated sample size was 122 patients per arm. To account for potential drop-out, we increased the sample size to 300 participants in total, with 150 patients in each study arm.

**Table 3 Tab3:** Participant timeline

	Study period							Follow-up
Time point	Screening	D0	D1	D2	D3	D4	D5	D28
Number of visits	1	2	3	4	5	6	7	8
Eligibility criteria	x							
Informed consent	x							
Allocation	x							
Demographic data		x						
APACHE II		x						
SOFA score		x						
Laboratory tests (total serum protein, albumin, prealbumin)		x					x	
Estimation of energy and protein target		x						
Administration of enteral nutrition			x	x	x	x	x	
Assessment of tolerance (diarrhea, vomiting, GRV, postpyloric nutrition)			x	x	x	x	x	
Assessment of complications			x	x	x	x	x	
Assessment of energetic and protein targets			x	x	x	x	x	
Assessment of hospital LOS, ICU LOS, and mortality								x

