## Assignment of interventions: blinding

### Who will be blinded {17a}

The study staff members and treating physicians and other staff will not be blinded, because of the impossibility of blinding while performing the study intervention. The data management group and statisticians will work with a pseudonymized data set.

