### Procedure for unblinding if needed {17b}

Not applicable.

This trial is not blinded.

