### Data management {19}

The study data will be entered online in an Internet-based database and collected from medical records. The study staff members will have access to the medical records of the patients. Investigators will be responsible for (1) screening of patients, (2) obtaining informed consent, (3) randomization, and (4) collecting study data and entering the data in the eCRF. The statistician will analyze the study data in cooperation with the principal investigator. The data will be stored for 15 years after completion of the study and then destroyed.

To promote data quality, the eCRFs of each participant will be reviewed by another member of the study team.

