## Statistical methods

### Statistical methods for primary and secondary outcomes {20a}

For analyses of study data, the intention-to-treat principle will be used.

For analyses of the primary outcome, the Kaplan-Meier curve, log-rank, or Wilcoxon test will be used. Standard descriptive statistics (i.e., number of available values, mean, SD, median, 25% and 75% quartiles, minimum and maximum) will be calculated for continuous variables. Categorical variables will be described by using tables of frequency. Secondary outcome measures will be compared between study groups with the *t* test or Mann-Whitney test as applicable, and the chi-square test will be used for categorical data. Differences in laboratory tests between different days of measurement will be analyzed with paired tests (paired *t* test or non-parametric Wilcoxon test). A Kaplan-Meier curve will be used to demonstrate 28-day mortality. A significance level of 5% will be used for all statistical tests. Confidence intervals will be presented as appropriate.

The data analyses will be performed after completion of the study. Interim analysis is not planned.

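### Intention-to-treat is promised in {20a}, but {20c} removes major deviators from the analysis at the principal investigator's case-by-case judgement in an unblinded trial

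*Protocol article*

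**What the plan says.** Section {20a} of the protocol article sets the principle without qualification: "For analyses of study data, the intention-to-treat principle will be used".

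Section {20c}, on non-adherence and missing data, makes three statements:

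- The consequence of a serious departure is removal: "Patients with major deviations from the study protocol will be excluded from the analysis".
- The person who decides, and the manner of deciding, are given as follows: "Protocol non-adherence will be assessed by the principal investigator case by case".
- There is no named set to which the removal could be confined: "No analysis populations are defined for this study".

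Three other sections bear on how the exclusion would work:

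- Section {17a}: "The study staff members and treating physicians and other staff will not be blinded". Section {17b} confirms: "This trial is not blinded". Only the data managers and statisticians are said to use a pseudonymised data set, which hides identity but not necessarily the arm.
- Section {19}: "The statistician will analyze the study data in cooperation with the principal investigator".
- Section {20b} plans no additional analyses.

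**The concern.** Intention-to-treat keeps every randomised patient in the assigned arm whatever happens to adherence afterwards. A rule that drops patients for what happened after randomisation is a different analysis. The article commits to both, so a reader of the results could not tell which one the primary comparison was meant to be.

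The exclusion matters more here than in some trials because the intervention and the outcome are recorded in the same quantity. The arms are defined by how feed is delivered and advanced, and the primary outcome is the day on which at least 80% of the planned feed has been given. Feed that was missed, or not advanced when the algorithm called for it, may be a deviation and can also delay the target. The two arms have different delivery procedures (an 18-hour infusion against six timed boluses), so such lapses need not be equally common in both. If exclusions are related to outcome, and more so if they also differ by arm, the comparison loses the protection of randomisation.

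**Working it through.** **Reading the text.** Could the exclusion in {20c} refer only to a secondary analysis? Three points say no. The sentence speaks of the analysis without qualification. The same section says that no analysis populations exist, so there is no per-protocol set for it to apply to. Section {20b} plans no further analyses. The primary comparison is therefore covered, and {20a} and {20c} conflict.

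**Size.** The article states no figure for exclusions, so there is nothing to reproduce. The following is an illustration.

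Inputs from the article: 150 patients per arm ({14}), significance level 5% and a log-rank test ({20a}; the log-rank is one of the two tests named there), time recorded in days ({12}), and a study period of days 1 to 5 ({11a}).

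Assumptions not in the article: a two-sided test; exponential times with median 2.5 days in both arms (midway between the day 2 and day 3 of the sample-size section); 5% or 10% of an arm excluded.

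The mechanism by arithmetic:

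- Probability of reaching the target by day 5: 1 − 2^(−5/2.5) = 0.75, so 112.5 of 150 are expected to reach it and 37.5 are not.
- Remove 8 non-reachers (about 5%) from one arm: 112.5/142 = 79.2% against 75%.
- Remove 15 non-reachers (10%): 112.5/135 = 83.3% against 75%.

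A difference of 4 to 8 percentage points thus appears where none exists.

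Type I error by simulation: times rounded up to whole days, censored at day 5, log-rank test with |z| > 1.96. Each cell gives the result of 3,000 simulated trials, then of a repeat with 10,000. The third row was run only with 10,000.

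| Who is excluded | 5% (8 per affected arm) | 10% (15 per affected arm) |
|---|---|---|
| Equal shares of both arms, unrelated to outcome | 5.0%, 4.8% | 4.9%, 5.5% |
| Equal numbers of non-reachers from both arms | 7.4%, 7.2% | 9.4%, 9.4% |
| One arm only; a quarter to a half of those excluded are non-reachers | 5.4 to 6.5% | 5.7 to 10.1% |
| One arm only; all excluded are non-reachers (worst case) | 13.6%, 13.5% | 35.8%, 35.4% |

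With nobody excluded the error is about 5%. Another repeat of the worst case at 10% gave 38%, so 35 to 38% is a fair statement of that cell.

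**Power if everyone is kept.** Take day 2 and day 3 as exponential medians (my assumption), so the hazard ratio is 1.5. The average probability of reaching the target by day 5 is (0.823 + 0.685)/2 = 0.754. All 300 patients give about 226 events, and power is Φ(√226/2 × ln 1.5 − 1.96) = Φ(1.09), about 86%. The 244 patients of the calculation before drop-out give about 184 events and Φ(0.79), about 79%. Keeping everyone does not reduce the planned number of events. Non-adherence may dilute the effect somewhat, but that is part of what an intention-to-treat comparison estimates.

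**The case against.** Several points can be made for the plan, and most of them limit the concern without removing it.

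- **Intolerance is not deviation.** A reader might infer that the rule would strip out patients who tolerate feeding poorly. The article does not support this. Sections {11a} and {11d} make lowering, holding or postponing feed, and moving to postpyloric feeding, part of the described intervention, and {11b} says so expressly. A patient who misses the target by that route has followed the protocol. What remains is feed missed or not advanced outside the algorithm, and nothing shows that this would fall only on patients who miss the target.
- **The large error rates are a worst case.** A reader might take 36% as the expected type I error. It requires every excluded patient to be a non-reacher and all of them to come from one arm. The other rows of the table are at least as plausible.
- **The drop-out allowance is not an exclusion rate.** Raising 244 to 300 patients allows for 56 losses (18.7%), but section {14} gives this for drop-out. It says nothing about how many deviators would be removed.
- **The principal investigator's knowledge.** That this person knows the arm is a fair inference from unblinded study staff. That the outcome is also known when deviations are judged is not stated.
- **Detail may sit elsewhere.** What counts as a major deviation, and when it is decided, is commonly left to an analysis plan. Its absence here is not the finding.

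The conflict itself stands. A separate analysis plan could follow only one of the two stated rules and would then contradict the other.

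**Conclusion.** The plan is wrong as written: {20a} and {20c} give incompatible rules for the primary analysis. Applying {20c} would mean that the result is not intention-to-treat, and the comparison would be open to selection after randomisation, because an unblinded, case-by-case judgement does nothing to keep exclusions unrelated to arm and outcome. The article shows that such bias is possible, not that it will occur.

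Under the stated assumptions the consequence runs from none (5 to 6%) through modest (7 to 10%) to serious (14% with 5% excluded, about 36% with 10%). The exclusion shares and the median are mine, so the range should be read as a whole. The contradiction does not depend on any of these numbers.

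**What to change.** Replace the exclusion sentence in {20c} with:

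> All randomised patients are included in the primary analysis in the arm to which they were assigned, regardless of adherence. Exclusion of patients with major deviations applies only to a secondary per-protocol sensitivity analysis, with the deviation criteria fixed before the data are analysed.

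The statement in {20c} that no analysis populations are defined, and the one in {20b} that no additional analysis is planned, need to be brought into line.

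This wording deliberately settles no more than the conflict. Sections {12} and {18a} start the clock at the beginning of enteral nutrition, so a randomised patient who never starts has no time zero. That case, and the handling of patients who stop early, need their own rule in the analysis plan. A reviewer masked to both arm and outcome is not required: departures from an infusion or bolus regimen can hardly be judged without seeing the regimen, and the delivered volume is the source of the outcome.

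The cost is a wording amendment and one extra sensitivity analysis. No additional patients or data are needed.

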### Plans to give access to the full protocol, participant level-data, and statistical code {31c}

Data sharing statement:

No later than 3 years after the collection of the 1-year postrandomization, we will deliver a completely deidentified data set to an appropriate data archive for sharing purposes.

Statistical codes will be archived in accordance with SOPs.

## Oversight and monitoring

### Composition of the coordinating center and trial steering committee {5d}

No coordinating center or a trial steering committee will be established.

### Composition of the data monitoring committee, its role, and reporting structure {21a}

Not applicable.

No data monitoring committee will be established. The study intervention is part of the standard care of critical care patients, and both modes of application of EN can be used interchangeably.

### Adverse event reporting and harms {22}

The formula of EN used in this study is approved for use in critically ill patients, and no severe adverse events relating to the components of this formula are expected.

Serious adverse events have been reported according to standard rules and standard operating procedures of the coordinating unit. All study participants will be monitored for potential adverse events associated with the administration of EN.

We expect the following adverse events to be associated with the administration of EV.
Tube malposition. Strategies to prevent gastric tube malposition are described in the “Intervention description {11a}” section of the protocol.Gastrointestinal complications (high GRV, diarrhea, or vomiting). Management of high GRV is described in the “Intervention description {11a}” section of the protocol. These complications are considered signs of EV intolerance, which result in a decreased rate/volume of EN administered.Refeeding syndrome. Strategies for prevention and management of refeeding syndrome (RFS) are part of the standard care in participating units. They include daily clinical and laboratory screening for RFS and standard medical management if RFS is diagnosed.

### Frequency and plans for auditing trial conduct {23}

Trial conduct will be audited by the Institutional Ethics Committee every 6 months during the study. The process of auditing will be independent of the investigator and sponsor.

### Plans for communicating important protocol amendments to relevant parties (e.g., trial participants, ethical committees) {25}

Any modifications to the protocol that may affect the conduct of the study, the potential benefits to the patient, or patient safety, including changes in study objectives, study design, patient population, sample sizes, study procedures, or significant administrative aspects, will require a formal amendment to the protocol. Any amendments will be agreed on and approved by the ethics committee before implementation, and the health authorities will be notified, in accordance with local regulations. The protocol amendment will be sent to all members of the study team by e-mail. All attending physicians and nurses of the study units will be acquainted with the amendment at a meeting. The invitation to the meeting will be sent by e-mail. The protocol of the study and its amendments will be available at each study unit.

## Dissemination plans {31a}

We intend to submit the results of the study to be published in a peer-reviewed international medical journal.

## Discussion

EN has been used in the treatment of critically ill patients for decades. Guidelines for its provision have been developed by several international societies [1, 11, 14] and are periodically updated. Although the body of evidence is growing, several controversies and uncertainties remain. Recent guidelines of the American Society for Parenteral and Enteral Nutrition (ASPEN) suggest that in high-risk patients and those shown to be intolerant to bolus gastric EN, the delivery of EN should be switched to continuous infusion [1]. This recommendation is based on expert consensus but is supported by very limited evidence. The studies in the analysis were small and performed on different patient populations [6, 8, 9, 15–18].

After the commencement of this study, new ESPEN guidelines on clinical nutrition in the intensive care unit were published. One recommendation is that continuous rather than bolus EN should be used. However, the authors assumed that the evidence on this issue is very limited. In a randomized clinical trial, intermittent feeding in comparison with continuous feeding has been found to result in no statistically significant difference in vomiting, abdominal distension, or diarrhea [19].. No significant differences in high GRV, abdominal distention, diarrhea, and vomiting in critically ill patients who received EF by bolus versus the continuous method have been reported [2]. A review of continuous and intermittent feeding has summarized the benefits and drawbacks of both feeding methods and found no evidence favoring either method with regard to metabolic, gastrointestinal, and organizational concerns [20].

Our protocol uses clinical signs of tolerance and GRV to determine the administration rate of EN. We use a volume of GRV > 500 mL as a sign of intolerance. In some studies, smaller volumes have been considered markers of intolerance [2]. Limitation or interruption of the administration of EN on the basis of lower GRV has been shown to lead to inadequate nutrition intake, and EN cessation is not recommended for GRV < 500 mL [1, 21, 22].

To promote EN tolerance, prokinetics will be used under the circumstances described in the “Relevant concomitant care permitted or prohibited during the trial {11d}” section of this protocol. Erythromycin or metoclopramide can be used. Both drugs are effective in decreasing feeding intolerance without increasing the rates of diarrhea and significant arrhythmias [23]. Metoclopramide has the same effectiveness regardless of the mode of administration, and the choice of a particular agent and mode of administration will be the responsibility of the attending physician [24]..

Regarding the primary outcome, the time to reach the energy target has been compared in two studies [6, 8]. After a detailed review of the study protocols, we have found that in both these studies, the increments of EN in the intermittent and continuous arm were set differently. In the case of optimal tolerance of EN, the energy target would have been reached at different time points, although the EN would have been started simultaneously in the bolus or continuous arm. Therefore, comparison of EN administration modes is problematic. In our study, we set the increments of EN so that the energy target is reached at the same time point regardless of whether EN is administered continuously or as a bolus. Therefore, both modes of EN administration are comparable regarding the primary outcome.

Aspiration of EN is a complication of EN administration. Objectively estimating aspiration is difficult. The method of coloring EN has been used in some studies. However, this method is currently not recommended for identification of aspiration because of potential adverse metabolic effects of the dye [25–27].

Aspiration of EN will be identified and noted in the medical record by nursing staff during standard airway care. This method of identification of EN aspiration is highly subjective and may be a potential source of bias.

In conclusion, we believe that this randomized trial will provide additional information regarding whether continuous or bolus feeding is associated with any differences in the tolerance and complication rate.

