### Intervention description {11a}

The position of the gastric tube will be verified by measurement of gastric pH or abdominal X-ray. Commercial isocaloric formula with a high content of whey-based protein will be used. To eliminate the effects of formula composition on primary and secondary outcomes of the study, the same enteral formula will be used in all patients included in both study arms. Energetic and protein targets will be estimated according to current guidelines, on the basis of body mass index (BMI) and actual body weight (ABW), as summarized in Table 1 [1]. The energy and protein targets will be determined by the study investigator. The study investigator will provide information to the nurse and attending physician regarding the arm of the study to which the patient was assigned, the time of initiation of EN, and the target rate and bolus volume.

Administration of EN begins no earlier than 6 am and no later than 6 pm if signs of intolerance are absent (see below) and the GRV is below 500 mL. Otherwise, the start of EN will be postponed to the time of the next GRV measurement.

EN will be administered in the first arm (CONT) with continuous infusion via an enteral pump with an infusion time of 18 h per day. During the infusion, the patient will be in a 30–40° head-up position. The initial rate of infusion will be set to 25 mL/h and gradually increased every 4 h according to clinical signs of intolerance and GRV measurements. Signs of intolerance will be considered if abdominal distension or pain, vomiting, or diarrhea occur, and if the GRV exceeds 500 mL.

The rate of infusion will be increased according to tolerance and GRV. If there is no sign of intolerance, and the GRV is < 250 mL in two consecutive measurements, the rate will be increased by 25 mL/h until the target rate is reached. If signs of intolerance are absent, and the GRV is 250–500 mL, the current rate will remain unchanged. If intolerance signs are observed, or the GRV is > 500 mL, the rate will be decreased to half until the next assessment of tolerance and GRV.

The daily dose of EN will be divided in the second arm (INT) into six portions administered in 4-h intervals via an enteral pump. The rate of the enteral pump will depend on the volume of the bolus. To avoid sudden gastric distension, the rate will increase with increasing bolus volume [4]. The rates of the enteral pump for particular volumes of EN are summarized in Table 2.

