During the infusion of EN, the patient will be in a 30–40° head-up position. After the administration is finished, the gastric tube will be rinsed with 20 mL of water. The initial volume of the bolus will be 80 mL and will be gradually increased every 4 h according to clinical signs of intolerance and GRV measurements. Signs of intolerance will be considered as abdominal distension or pain, vomiting, diarrhea, and a GRV exceeding 500 mL.

The rate of infusion will be increased according to tolerance and GRV. If there is no sign of intolerance and the GRV is < 250 mL in two consecutive measurements, the volume will be increased by 80 mL/h until the target volume is reached. If intolerance signs are absent and the GRV is 250–500 mL, the current volume of the bolus will remain unchanged. If intolerance signs or a GRV > 500 mL is observed, the volume will be decreased to half until the next assessment of tolerance and GRV.

Measurement of GRV will be performed throughout the entire study period (days 1–5) in 4-h intervals with a 150-mL syringe used for aspiration of gastric content. Volumes lower than 150 mL will be returned to the stomach, and larger amounts will be discarded.

**Table 1 Tab1:** Energy and protein targets

BMI	Energy	BMI	Protein
< 30	25–30 kcal/kg of ABW/24 h	< 30	1.2–2 g/kg ABW/24 h
30–50	11–14 kcal/kg of ABW/24 h	30–40	2 g/kg ABW/24 h
–	–	> 40	2–2.5 g/kg ABW/24 h

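### The protocol's own feeding figures do not give the equal time to target that the Discussion claims, so the schedule alone can move the primary endpoint day

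*Protocol article*

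**What the plan says.** The Discussion faults two earlier studies because their increments would have brought the arms to target at different times even with optimal tolerance. Of this trial it says "we set the increments of EN so that the energy target is reached at the same time point" whichever mode is used, and infers that the modes can be compared on the primary outcome.

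Intervention description {11a} sets the schedules:

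- CONT is fed "with continuous infusion via an enteral pump with an infusion time of 18 h per day". "The initial rate of infusion will be set to 25 mL/h and gradually increased every 4 h", and when tolerance allows "the rate will be increased by 25 mL/h until the target rate is reached".
- INT receives the daily dose "into six portions administered in 4-h intervals via an enteral pump", starting at 80 mL per bolus. When tolerance allows, "the volume will be increased by 80 mL/h until the target volume is reached".
- In both arms a step up needs two consecutive residual volumes below 250 mL, measured every 4 h.

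Outcomes {12} defines the primary endpoint as the time to delivery of at least 80% of target energy, reported in whole days. Sample size {14} plans for a 1-day difference (day 2 against day 3).

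**The concern.** The equal-time sentence is a factual statement about the design, and it carries the interpretation of the primary result. If the arms would reach 80% of target together under perfect tolerance, any observed difference can be put down to tolerance of the mode. If they would not, a difference may arise from the step sizes and the daily pause, or a real advantage of CONT may be masked by them. The endpoint is counted in whole days and the planned effect is one day, so a modest difference in delivered volume can change the recorded outcome of a patient near the 80% line.

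**Working it through.** **Inputs.** From {11a}: CONT starts at 25 mL/h, steps by 25 mL/h and runs 18 h per day; INT starts at 80 mL, steps by 80 mL and gets six boluses per day, 4 h apart; feeding starts between 06:00 and 18:00. From Outcomes {12}: threshold 80%. Assumptions: 1 kcal/mL (the text says only that the formula is isocaloric), no intolerance, the CONT pause taken as one 6-h block, and the bolus step read as 80 mL. That last reading follows Table 2, where bolus volumes rise by 80 mL up to 400 mL and pump rates stand in a separate column.

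**The stated figure.** The Discussion implies a difference of zero under optimal tolerance. This is not reproduced.

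**Step size.** CONT: 25 × 18 = 450 mL/day per step. INT: 80 × 6 = 480 mL/day per step. Ratio 480/450 = 1.067.

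| Level | CONT mL/day | INT mL/day |
|---|---|---|
| 1 | 450 | 480 |
| 2 | 900 | 960 |
| 3 | 1350 | 1440 |
| 4 | 1800 | 1920 |
| 5 | 2250 | 2400 |

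A 1900 mL target needs five levels in CONT (1900/18 = 105.6 mL/h) and four in INT (1900/6 = 316.7 mL). With a step every 4 h, full rate comes at 16 h and 12 h.

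**Daily profile, 1500 kcal, step every 4 h.** Full rate is 1500/18 = 83.3 mL/h in CONT; full bolus is 1500/6 = 250 mL in INT.

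- CONT, first 24 h (18 h of feeding, then the pause): 25×4 + 50×4 + 75×4 + 83.3×4 + 83.3×2 = 100 + 200 + 300 + 333 + 167 = 1100 mL, or 73%.
- INT, first 24 h: 80 + 160 + 240 + 250 + 250 + 250 = 1230 mL, or 82%.

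If a day is 24 h from the start of feeding, INT meets the endpoint on day 1 and CONT on day 2. On these assumptions the same holds for every target from 1230 to 1600 kcal.

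If the day is the calendar day, feeding starts at 06:00 and CONT pauses from midnight to 06:00, day 1 is 18 h long. CONT has delivered 1100 mL (73%) and INT, with five boluses, 80 + 160 + 240 + 250 + 250 = 980 mL (65%). Both meet the endpoint on day 2. While its pump runs CONT is ahead; INT overtakes during the pause. That is why the day boundary matters so much.

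**Range over what the article leaves open.** Both arms were simulated hour by hour for targets of 1000–2700 kcal (steps of 25) and starts from 06:00 to 18:00 (every 2 h). There were 36 readings: a step every 4 h or every 8 h (both fit a 4-hourly review that needs two low measurements); pause after the first 18 h, at 00:00–06:00 or at 22:00–04:00; steps allowed or not during the pause; day as 24 h from start, calendar day or 06:00–06:00. Ranges are over the pause readings.

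| Step | Day | CONT one day later | INT one day later | Mean shift, CONT − INT (days) |
|---|---|---|---|---|
| 4 h | 24 h from start | 16–23% | 0–2% | 0.15 to 0.23 |
| 4 h | calendar | 0–15% | 0–2% | −0.02 to 0.15 |
| 4 h | 06:00–06:00 | 6–16% | 0–4% | 0.02 to 0.16 |
| 8 h | 24 h from start | 4–36% | 0–1% | 0.03 to 0.36 |
| 8 h | calendar | 1–40% | 0–3% | −0.02 to 0.40 |
| 8 h | 06:00–06:00 | 5–53% | 0–0.2% | 0.05 to 0.53 |

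At least one combination of target and start time changes endpoint day in 35 of the 36 readings. The exception is calendar days with 4-h steps, a 22:00–04:00 pause and steps allowed during it. The percentages weight targets and start times equally; they are not forecasts for the trial population.

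**The case against.** The increments are nearly matched. They differ by 6.7%, and for about 81% of targets between 1000 and 2700 kcal both arms need the same number of levels. In 35 of the 36 readings most combinations fall on the same endpoint day. The trial is labelled explorative, the claim is one passage of the Discussion, and the randomised comparison of the two regimens as specified remains valid. All of this stands. It limits the size of the problem but does not make the equal-time statement true.

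A reader might infer that part of any difference the trial finds must come from the schedule, or that the schedule alone reproduces the whole planned 1-day effect. The document does not support either. The full-day shift applies to individual patients in a band of targets under particular readings; it is not a shift of the trial mean. No distribution of weights or targets is given, and the 1500 kcal example moves day 1 to day 2, whereas the plan assumes day 2 against day 3. Some readings show no shift or a slight one towards CONT. If CONT proved faster, the schedule would more often hide part of its advantage than create it.

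It may also be said that Table 2 settles the mL/h unit. It probably does, and nothing above depends on it, but the text and the table still disagree.

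**Conclusion.** The point holds in a limited form. The Discussion ascribes to the design a property that the figures in {11a} do not give: 450 against 480 mL/day per step, and 18 h against 24 h of daily coverage. This does not depend on where the pause falls. Under perfect tolerance and 1 kcal/mL the schedule can move the primary endpoint day, mostly in favour of INT. The mean shift is about 0 to 0.5 day, with a full day for some targets (such as 1500 kcal with 4-h steps and days counted from the start of feeding) and essentially none under some calendar-day readings. Confidence is high that the statement is wrong as written and low about the size in this trial, because the pause, the step rule and the day definition are not fixed in the article. What fails is the attribution of a difference to mode of administration alone, not the comparison of the two regimens.

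**What to change.** 1. Reconcile Intervention description {11a} with the Discussion: the 18 h × 25 mL/h and 6 × 80 mL schedules, and the mL/h unit on the bolus step against Table 2. Which figures are right is for the investigators to state; no feeding rule is proposed here.
2. Delete or correct the statement that the target is reached at the same time in both arms, and the comparability conclusion drawn from it.
3. Word the primary conclusion as a comparison of the two feeding schedules as specified, not of continuous against intermittent administration alone.
4. Optional support: once the step rule, pause and day definition actually in use are stated, report by arm and energy target the earliest endpoint day attainable under perfect tolerance. This cannot be computed from {11a} as it stands.

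The day should not be redefined as 24 h from the start of feeding for this purpose. With 4-h steps that would raise the share of combinations with CONT a day later from 0–15% (calendar day) to 16–23%, and it would change a primary endpoint definition in an unblinded trial with 100 patients already randomised.

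Items 1 to 3 cost only wording, and item 4 is one table of deterministic arithmetic. The downside is a weaker claim of comparability, including against the earlier studies that the Discussion criticises.
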